# Trauma-focused treatments for refugee children: study protocol for a randomized controlled trial of the effectiveness of KIDNET versus EMDR therapy versus a waitlist control group (KIEM)

**DOI:** 10.1186/s13063-022-06178-z

**Published:** 2022-04-23

**Keywords:** Psychotrauma, EMDR, KIDNET, Therapy, Refugees, Children, Posttraumatic stress disorder, Randomized controlled trial

## Abstract

**Background:**

Prevalence of posttraumatic stress disorder (PTSD) in refugees is reportedly higher in comparison to the general population. Refugee children specifically are often coping with trauma and loss and are at risk for mental health difficulties. With staggering numbers of people seeking refuge around the world and 50% being 18 years or younger, research examining the effects of trauma-focused therapies for refugee children with PTSD is highly needed. Both Eye Movement Desensitization and Reprocessing (EMDR) therapy and the child version of Narrative Exposure Therapy (KIDNET) have been used for refugees, although these treatment methods have not been systematically compared. The aim of the current study is to investigate the effectiveness of EMDR and KIDNET, compared to a waitlist control group and with each other, offered to refugee children.

**Methods:**

A randomized controlled three-arm trial has been designed. The primary outcome is PTSD diagnosis and symptom severity assessed with the Clinician-Administered PTSD Scale for Children DSM5 (CAPS-CA-5) at baseline (T1), 1 month post-treatment, or after 8 weeks of waiting (T2) and 3 months follow-up (T3). Additionally, instruments to assess posttraumatic stress symptoms, behavioral and emotional problems, and quality of life perception in children aged 8–18 are conducted at T1, T2, and T3.

**Discussion:**

This is the first RCT that examines the effectiveness of EMDR and KIDNET in refugee children aged 8–18 years specifically, compared to a waitlist control group intended to reduce PTSD diagnosis and severity of posttraumatic stress symptoms and comorbid complaints in a growing and challenging population.

**Trial registration:**

Dutch Trial Register NL40769. Retrospectively registered on June 16, 2021.

## Background and rationale

In 2015, European countries faced unusually high arrivals of more than 1.2 million asylum seekers [1]. About half of this population consists of minors. Many of them have been exposed to multiple stressful experiences, such as war, violence, separation, and migration, and are facing continuing challenging living circumstances and uncertainty [2, 3]. At the same time, they often have parents undergoing similar or higher levels of stress. Parental stress has been associated with an increase of psychosocial problems, anxiety and depression symptoms in children, and attachment-related difficulties in infants [4, 5].

Although refugee children and adolescents show impressive resilience and flexibility, they are highly vulnerable to the effect of prolonged traumatic stress due to their age and developmental stage [6]. Despite variations in prevalence rates, there is a consensus that mental health problems, such as PTSD, are higher in refugee children than in general populations [7]. A recent systematic review reports prevalence rates of posttraumatic stress disorder (PTSD) between 19.0 and 52.7% among young refugees and asylum seekers in European countries [8]. Untreated PTSD can lead to the development of anxiety disorders such as generalized anxiety disorder, panic disorder, or mood disorders such as depression or substance use disorders [9]. Ultimately, children’s personality development may be affected by early traumatization. To prevent these harmful long-term effects, effective and timely treatment of PTSD is necessary.

While increasing studies evaluate the effectiveness of psychological interventions for traumatized children [10, 11], hardly any attention is being devoted to the application of interventions to traumatized refugee children specifically. Several studies on the effects of trauma-focused cognitive behavioral therapy (TF-CBT) report a decrease in trauma-related symptoms in children from war-affected countries after TF-CBT, compared to a control group [12–15]. Although results are promising, intervention studies focusing on traumatized refugee children are not only scarce, but also often methodologically weak [16]. As traumatized refugee children and adolescents are increasingly being identified as a specific group within the mental health field and their number is growing, it is needed to shed more light on the effects of trauma-focused treatment for this population. In this paper, a randomized controlled trial (RCT) is described focusing on the effectiveness of two trauma-focused treatments, KIDNET and EMDR, compared to a waitlist control group in reducing PTSD symptoms and comorbid symptoms in refugee children. In Tables 1 and 2, an overview of the studies on EMDR and KIDNET in refugee children is presented.

**Table 1 Tab1:** Studies on the effectivity of (KID)NET with refugee children

Study	Studied population	*N*	Study design	Treatment	Number and duration of sessions	Instrument PTSD	Measure points	Results
Catani et al. (2009) [17]	Internally displaced children aged 8–14 in Sri Lanka	31	RCT	KIDNET vs MED-RELAX	6 sessions of 60–90 min	UPID	Pretreatment and 1-month and 6-month follow-up	Significant reduction of PTSD symptoms in both conditions, no significant differences between conditions were found. Effect sizes (Cohen’s *d*) for the KIDNET group were 1.76 at post-test and 1.96 at 6 months follow-up.
Ertl et al. (2011) [18]	Former child soldiers aged 12–25 in Uganda	85	RCT	(KID)NET vs academic catch-up program vs waitlist	8 sessions of 90–120 min	CAPS, revised version for DSM-IV	Pretreatment and 3-month, 6-month, and 12-month follow-up	Significant reduction of PTSD symptoms, superiority of (KID)NET (Cohen’s *d* = 1.80).
Onyut et al. (2005) [19]	Refugee children aged 13–17 from Somali in Uganda	6	Pre-post study	KIDNET	4–6 sessions of 1–2 h	CIDI (PDS + HSCL for screening)	Pre-treatment, 4 weeks and 9-month follow-up	After 9 months, four of the six participants no longer met the criteria for PTSD.
Peltonen et al. (2019) [20]	Refugee children and children with experiences of family violence aged 9–17 living in Finland	50	RCT	KIDNET vs TAU	7–10 sessions of 90 min	CRIES-13	pre-, mid-, and posttreatment and 3-month follow-up	No evidence was found for superior effects of NET versus TAU on reduction in PTSD symptoms. There was a decrease in PTSD symptoms regardless of treatment condition; however, this decrease was significant in the NET group only. The effect sizes (Cohen’s *d*) were large in NET (0.83), but small in TAU (0.37)
Ruf et al. (2010) [21]	Refugee children aged 7–16 in Germany	26	RCT	KIDNET vs waitlist	7–8 sessions of 90–120 min	UPID	Pretreatment, 4-weeks, 6-month, and 12-month follow-up	The KIDNET-group (ES=1.9), but not the waitlist (ES=0.3), showed clinically relevant and significant reduction in PTSD symptoms.
Said et al. (2020) [22]	UCM aged 16–17 from Sudan, Vietnam, and Albania in the UK	4	Pre-post study	KIDNET	9–20 sessions	CRIES-8 + CPSS-5	pre-, start-, mid-, and posttreatment	PTSD symptoms were below the clinical range after treatment. All three participants who completed KIDNET met the criteria for reliable improvement.
Schauer et al. (2004) [23]	Refugee child aged 13 from Somalia in Uganda	1	Case study	KID-NET	4 sessions of 60–90 min	PDS	Pretreatment and at 6-month follow-up	The post-test showed that the symptoms decreased to a degree below the diagnostic threshold for PTSD.

Note: *UPID* UCLA PTSD index for DSM-IV, *CIDI* Composite International Diagnostic Interview, *PDS* The Posttraumatic Diagnostic Scale, *HSCL* the Hopkins Symptom Checklist-25, *CRIES* Child Revised Impact of Events Scale, *CPSS-5* Child PTSD Symptom Scale

**Table 2 Tab2:** Studies on Effectivity of EMDR With Refugee Children

Study	Studied population	N	Study design	Treatment	Number and duration of sessions	Instrument PTSD	Measure points	Results
Oras et al. (2004) [24]	Refugee children aged 8–16 in Sweden	13	Pre-post study	Age 8–13: EMDR + play therapy Age 13+: EMDR + conversational therapy	Total 5–25 sessions of which 1–6 sessions of EMDR	PTSS-C, GAF	Pre- and posttreatment	A significant improvement was found in the functioning level and all PTSS-C scales. The improvement in the functioning level was significantly correlated with the reduction of the PTSD-non-related and the depression symptoms, but not with the PTSD-related symptoms.
Wadaa et al. (2010) [25]	Refugee children aged 7–12 from Iraq in Malaysia	37	(Nonrandom) controlled trial	EMDR vs no treatment	12 sessions	UPID	Pre- and posttreatment	EMDR, but not the control group, was effective in reducing PTSD symptoms. (Hedges’s *g* = 3.46*)

Note: *PTSS-C* The Posttraumatic Stress Symptom Scale for Children, *GAF* Global Assessment of Functioning, *UPID* UCLA PTSD index for DSM-IV

*Effect size calculated by author

### Child version of Narrative Exposure Therapy (KIDNET)

Narrative Exposure Therapy (NET), originally developed in the context of a refugee camp [26, 27], is an evidence-based trauma treatment developed especially for multiple traumatized people exposed to repeated and various traumatic stressors, such as war, torture, rape, childhood abuse, and other forms of multiple and organized violence [28]. While initially designed for adults, adaptations were made from the start for the use of NET in children 8 years and older: KIDNET [19, 23]. KIDNET is focused on reducing posttraumatic stress symptoms by the technique of narrative exposure. By working through the child’s biography and focusing on the autobiographical elaboration of traumatic experiences, KIDNET facilitates processing traumatic memories of traumatic experiences from the child’s recent past [29]. The effectiveness of NET in reducing PTSD symptoms in adults has been established in several randomized controlled trials and several studies show promising results regarding the effectiveness of KIDNET in treating children with PTSD [30, 31].

Seven studies evaluated the effects of KIDNET in treating refugee children with PTSD symptoms (Table 1). Promising evidence regarding the effectiveness of KIDNET in refugee children with PTSD symptoms has been found in four RCTs, two pre- to posttest studies, and one case study [17–23]. In all studies, a reduction of PTSD symptoms was found after receiving KIDNET. KIDNET was compared to meditation-relaxation, treatment as usual (TAU), a waitlist control group, and with an academic catch-up program. The number of participants in the studies ranged from 1 to 85. Some limitations of the study designs included a lack of a control group in some studies, a small sample size, and the absence of a clinical interview in most studies. The CAPS-CA, seen as the golden standard for measuring PTSD in children, has been only administered in one study.

### Eye Movement Desensitization Reprocessing (EMDR)

EMDR is an evidence-based trauma treatment for processing traumatic memories in children and adults [32]. The core feature of EMDR is that an individual recalls a distressing memory while also performing a secondary task (dual taxation), usually engaging in sets of saccadic eye movements. Both tasks compete for limited resources of the working memory. As a consequence, the distressing memory becomes less vivid and emotional [33]. The effectiveness of EMDR in reducing PTSD symptoms in adults has been established in several randomized controlled trials [34]. Moreover, many studies show promising results regarding the effectiveness of EMDR in treating children with PTSD [35]. While EMDR has been recommended by international guidelines, only two studies have been known to us that assess the effects of individual EMDR treatment in refugee children with PTSD symptoms (Table 2). The results of the two studies demonstrated significant improvement on PTSD symptoms [24, 25]. However, serious disadvantages to the study designs included a small sample size, the lack of randomization, lack of self-report instruments, restricted age range of participants, and possible bias in assigning children to the treatment conditions (unequal subsample sizes).

### Objectives of the current trial

The aim of the current study is to investigate the efficacy of both EMDR and KIDNET compared to a waitlist control group. The research questions are:
Is EMDR effective in decreasing PTSD and posttraumatic stress symptoms, decreasing behavioral and emotional symptoms, and improving quality of life in refugee children and adolescents, compared to a waitlist control group?

We hypothesize that EMDR is more effective in reducing PTSD and posttraumatic stress symptoms, behavioral and emotional symptoms, and improving quality of life in refugee children and adolescents, compared to a waitlist control group.
2)Is KIDNET effective in decreasing PTSD and posttraumatic stress symptoms, decreasing behavioral and emotional symptoms, and improving quality of life in refugee children and adolescents compared to a waitlist control group?

We hypothesize that KIDNET is more effective in reducing PTSD and posttraumatic stress symptoms, behavioral and emotional symptoms, and improving quality of life in refugee children and adolescents, compared to a waitlist control group.
3)Is there a difference in effectivity between EMDR and KIDNET?

We hypothesize that both interventions (EMDR and KIDNET) are effective in reducing post-traumatic stress symptoms. Therefore, we do not expect (large) differences in effectiveness between the two interventions and hypothesize that both interventions equally reach efficacy in refugee children aged 8–18 years. However, this comparison has not been done before, in case there is a small difference in effectiveness, we aim to detect it.

## Methods

### Trial design

A multicenter, randomized controlled trial comparing KIDNET and EMDR to a waitlist control group at various locations in the Netherlands will be conducted. Refugee children (*N*=93) between 8 up to and including 18 years of age will be randomly assigned to either EMDR (*n*=31), KIDNET (*n*=31), or a waitlist control group (*n*=31). When initially assigned to a treatment condition, participants and one of their parents or caregivers will be assessed three times: at intake (T1; maximum of 4 weeks before the first treatment session), at T2 (4 weeks after the last session), and T3 (3 months after the last session). Participants initially assigned to the waitlist control group will be assessed four times: at intake (T1) and after the waitlist period of 8 weeks (T2). Hereafter, the second randomization takes place and participants will be assigned to EMDR or KIDNET. T3 will be administered 4 weeks after the last session and T4 3 months after the last session. In the period between the last treatment session and follow-up, no trauma-focused treatment will be offered. Figure 1 depicts the flowchart of the study.

**Fig. 1 Fig1:**
[figure not shown]
Adapted CONSORT flow diagram, illustrating the study design, the flow of participants, and the planned assessments

### Study setting

Participants will be recruited through various channels, e.g., primary schools, high schools, international transitional classes in the Netherlands (ISK; a class for students between 12 and 18 who are recently residing in the Netherlands and speak little or no Dutch), general practitioners, centers for youth and family, and posts published through social media. Additionally, participants will be recruited in two outpatient clinics: (1) ARQ Centrum’45 (the Dutch national center for specialist diagnostics and treatment of people with (complex) psychotrauma complaints) and (2) I-psy Youth and Family (part of a specialist center in intercultural psychiatry). Assessments and treatment sessions will be carried out at various locations in the Netherlands; therapists travel to the living location or a location nearby the residency of the participants (and suitable for therapy, guaranteeing privacy for instance).

### Participants

#### Eligibility criteria

Eligible participants for this study must meet all following criteria: (1) between 8 and up to and including 18 years old and (2) partial or full PTSD diagnosis as reported by the child (interviewed with the Clinician-Administered PTSD Scale for DSM5 - Child/Adolescent Version (CAPS-CA-5; 36). Partial PTSD is defined as either fulfilling three of the four symptom clusters or one symptom present in each of the four symptom clusters. Participants will be included when they (3) are accompanied by at least one caregiver and (4) applied for asylum in the Netherlands or are residing in the Netherlands since January 2015 or later. A potential participant who meets any of the following criteria will be excluded from participation in this study: (1) estimated intelligence level (< 80), (2) acute interfering psychiatric disorder in need for treatment first, (4) brain damage, (5) acute threat of deportation or moving within intervention period, (6) anti-epileptic and neuro epileptic medication, or (7) current severe substance abuse.

### Therapists

All therapists are certified clinical psychologists, with a broad experience in treating refugee children and families and sufficient training in both active treatment conditions. Each therapist received a 4-day basic training on NET by official NET trainers and additionally must have completed a minimum of one full KIDNET treatment under supervision. In addition, each therapist giving treatment in this study received a 9-day training level 1 and level 2 according to the standards of EMDR Europe.

### Procedure

When a child is identified as a potential participant an introductory meeting is planned with the caregiver(s), the child, a member of the research team, and, if needed, an intercultural mediator. An Eritrean and Syrian intercultural mediator are part of the research team. In addition to translation/interpretation, it is expected that they may increase the trust of the participants by sharing their cultural background, can explain the study in their native language, and discuss stigma related to the use of mental healthcare. The second meeting, after obtaining informed consent, consists of further intake questions and collecting T1 data. When the CAPS-CA-5 has been administered and when the participant meets the inclusion criteria, a participant number is assigned. Then, the therapist is chosen based on availability. Hereafter, the participant will be randomly assigned to the EMDR condition, KIDNET condition, or the waitlist control group. In this way, randomization will occur across therapists. In case of a treatment condition (EMDR or KIDNET), the first session starts within 4 weeks after T1. In the case of a crisis, a child psychiatrist is available for consultation—as is a normal procedure during treatment.

#### Informed consent, randomization, and blinding

During the intake, the assessor explains the aim, method, benefits, and potential hazards of the study. The child and his/her legal guardian will then receive the informed consent (also available in Arabic and English). When the child (12 years and older) and his/her legal guardian agree to participate, the assessor obtains informed consent. When a child meets the inclusion criteria, an independent colleague of ARQ Centrum’45 is contacted and uses random allocation software for the random allocation of the participants to EMDR, KIDNET, or the waitlist control group. Random allocation is performed using a randomized block design with variable block sizes and an allocation ratio of 1:1:1. After the allocation is known, the independent colleague will inform the research coordinator. Hereafter, the research coordinator will inform the therapist about the allocation. Neither therapists nor study participants can be blinded to the treatment condition given the nature of the interventions. Independent members of the research team will administer T1–T4 assessments and remain blinded to the two treatment allocations (EMDR and KIDNET). Statistical analyzes will not start until the final assessment has been done. Hereafter, data analysts will no longer be blinded for the treatment allocation.

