#### Primary outcomes

##### Posttraumatic stress disorder and symptoms

At baseline, the LEC-5 will be administered to register the number and type of traumatic events the child was exposed to. To assess the presence of a (partial) PTSD diagnosis and symptom severity the CAPS-CA-5 for DSM5 will be administered. The CAPS-CA-5 is a 30-item structured clinical interview assessing PTSD symptoms based upon DSM5 criteria for children and adolescents aged seven and above. Symptoms in relation to the past month are examined. Symptom severity ratings are based on symptom frequency and intensity, with a severity score of two or higher indicating the presence of a symptom. CAPS-CA-5 can be administered reliably by different interviewers, with a kappa coefficient of .75 for the Dutch (DSM-IV) version [45] and .80 for the English DSM5 version [46]. The Dutch CAPS-5 is a carefully translated instrument with adequate psychometric properties [47].

Furthermore, both the child version and the parent version of the CRIES-13 will be administered. The CRIES-13 is a brief self-report measure to screen children aged 8 years and above for the severity of PTSD symptoms. The CRIES-13 consists of 13 items to assess intrusion, avoidance, and hyperarousal. The CRIES-13 child version has demonstrated good reliability among war-affected children and adolescents [42]. A study evaluating the reliability and validity of the CRIES-13 child version in a large clinically referred sample in the Netherlands (*n*=395) reported an internal consistency using Cronbach’s *α* of .89 and a test-retest reliability coefficient of .85 [48].

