### Project organization

The Trial Steering team is meeting three times a year to assure protocol adherence, oversee conduct and process as well as to exchange their expertise about running an RCT. This team consists of professors and health care professionals, among which one expert on KIDNET, one expert on EMDR applied to children, one expert on the CAPS-CA-5, and a colleague from I-psy Youth and Family. In addition, there is one team providing day-to-day support for the trial. This team consists of six people (one professor/clinical psychologist, two cultural mediators, two assessors, one PhD student/assessor). This team is meeting once every 2 weeks and is responsible for the assessments, local organization, recruitment of participants, assessments, and taking informed consent.

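### Assessor masking is stated only for EMDR versus KIDNET, so the interviewer-rated CAPS-CA-5 at T2 has no stated protection against detection bias in the two waitlist contrasts

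*Protocol article*

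**What the plan says.** The section on informed consent, randomization and blinding describes three-arm allocation: an independent colleague "uses random allocation software for the random allocation of the participants to EMDR, KIDNET, or the waitlist control group". The same paragraph says "Neither therapists nor study participants can be blinded to the treatment condition given the nature of the interventions", and that the team members who administer T1 to T4 "remain blinded to the two treatment allocations (EMDR and KIDNET". The waitlist appears in the allocation sentence but not in the masking sentence. Elsewhere, the section on generalizability says only that assessors are independent.

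In the abstract, "The primary outcome is PTSD diagnosis and symptom severity assessed with the Clinician-Administered PTSD Scale for Children DSM5 (CAPS-CA-5". Under the primary outcomes, "The CAPS-CA-5 is a 30-item structured clinical interview assessing PTSD symptoms", with severity rated from frequency and intensity.

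The first two research questions set each therapy against the waitlist. The statistical analyses section tests them with T1 and T2 as the time factor. The Procedure section places T1 before randomisation.

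The project organization section describes a day-to-day team that includes "two assessors, one PhD student/assessor". That team meets every two weeks and also handles recruitment and local organisation.

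**The concern.** A severity score from a clinical interview involves judgement. A rater who knows, or can guess, that a child is still waiting may score symptoms higher than for a child known to have finished therapy. That error runs in the direction of hypotheses 1 and 2. T1 is rated before allocation, so the whole exposure falls on T2.

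The stated masking protects EMDR versus KIDNET, where the protocol expects no large difference. It is silent on the two contrasts where a clear difference is expected. A later report that simply cites independent, blinded assessors would lead readers to credit the waitlist results with a protection that the protocol does not describe.

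**Working it through.** No figure in the plan is at stake, so the first two steps compare the text with itself and the third is an illustration.

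**1. Scope of masking**

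| Contrast | Visits analysed | Assessor masking stated? |
|---|---|---|
| EMDR vs waitlist | T1, T2 | No |
| KIDNET vs waitlist | T1, T2 | No |
| EMDR vs KIDNET | pre-treatment, post-treatment, follow-up | Yes |

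**2. Can the schedule reveal the arm at T2?** The visit has the same label in every arm, but not the same timing.
- Waitlist: T2 follows 8 weeks of waiting (Trial design; Waitlist control group).
- Therapy: the first session is within 4 weeks of T1 (Procedure), there are up to eight weekly sessions (EMDR; KIDNET), and T2 is 4 weeks after the last one (Trial design). Eight weekly sessions span 7 weeks from first to last. T2 then falls between 0 + 7 + 4 = 11 and 4 + 7 + 4 = 15 weeks after T1.
- Early completion shortens this. Five sessions starting at once give 0 + 4 + 4 = 8 weeks, the same as the waitlist.

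Elapsed time is therefore a strong cue for a full course of therapy, but not a certain one. An assessor who did T1, or who knows its date, can use it.

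**3. Illustration of size.** Inputs from the sample size section: 26 per arm, correlation r = 0.40, two-sided alpha 0.05. Assumption, not in the documents: an average shift b of 0.1, 0.2 or 0.3 SD at T2 in favour of therapy, with no true effect.
- SD of the T1-T2 change = sqrt(2(1 - r)) = sqrt(2 x 0.60) = 1.095 SD.
- Standard error of the difference between two arms = 1.095 x sqrt(2/26) = 0.304 SD.
- Degrees of freedom = 2 x 26 - 2 = 50; critical t = 2.009.
- Noncentrality = b / 0.304. The rejection rate is the probability that a noncentral t exceeds the critical value in either direction.

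| Assumed shift b | Noncentrality | Rejection rate, 26 per arm | Rejection rate, 31 per arm |
|---|---|---|---|
| 0.1 SD | 0.329 | 6.2% | 6.4% |
| 0.2 SD | 0.658 | 9.9% | 10.9% |
| 0.3 SD | 0.987 | 16.2% | 18.6% |

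The noncentrality column is for 26 per arm. The three-group time-by-treatment test with 26 per arm, with the same shift separating both therapy arms from the waitlist, gives nearly the same picture: 6.1%, 9.4% and 15.5%.

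**The case against.** The strongest reply is that the protocol never says assessors know who is waiting. Allocation passes from the independent colleague to the research coordinator and then to the therapist, and assessors are not in that chain. This stands. A reader might infer from the narrow wording that assessors are told who is on the waitlist, but the documents do not say so. What they support is that masking to the waitlist is not stated and that the timing can undo it.

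Other tempting readings go too far:
- **Visit labels.** The waitlist arm has a T4, and its T3 means something different from T3 in the therapy arms. Those labels diverge only after T2, so they cannot affect the waitlist contrasts.
- **Analysts.** The same section says "Hereafter, data analysts will no longer be blinded for the treatment allocation", once the final assessment is done. One might conclude that analysis choices are still open at that point. Such choices commonly sit in a statistical analysis plan that is not shown, so the text does not support this.
- **Sizing.** The waitlist contrasts are not the only ones sized. EMDR versus KIDNET has its own calculation, with 39 per arm, and no comparison is labelled primary.

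It can also be said that the CRIES-13 is listed under the primary outcomes: "The CRIES-13 is a brief self-report measure to screen children aged 8 years and above for the severity of PTSD symptoms". It avoids the interviewer's judgement, but the children and caregivers who complete it know their arm. It is not a clean substitute.

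Finally, children may disclose their status, and recruitment was due to end on 30 June 2022, with this protocol version dated March 2022. Both points limit what a change can achieve. Neither removes the need to state the scope of masking correctly.

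**Conclusion.** The concern holds in a limited form. The protocol states assessor masking for one of its three contrasts. For the two waitlist contrasts, the interviewer-rated CAPS-CA-5 at T2 has no stated masking, and the schedule can reveal the arm. EMDR versus KIDNET is covered by the masking as written.

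The size is unknown. The range of about 6 to 16% for a nominal 5% pairwise test rests entirely on an assumed shift of 0.1 to 0.3 SD, with 26 per arm and r = 0.40. It shows what a modest bias could do and does not estimate what has happened. The trial is not invalidated, but its waitlist results should not be presented as fully assessor-blinded on this text.

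**What to change.** Extend assessor masking to all three conditions for every T2 visit still to come:
- The research coordinator, who already holds the allocation, books the visit.
- One of the three existing assessors who did not see the child at T1 conducts it, without being given the allocation or the T1 date. The protocol does not say whether the coordinator is also an assessor; anyone who knows the allocation should not rate.
- Child and caregiver are asked beforehand not to mention treatment or waiting.
- After scoring the CAPS-CA-5, the assessor records a guess of the arm.

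Report the guesses by arm. State that T2 visits already completed were masked, as far as the protocol says, only between EMDR and KIDNET. If assessors were in fact also kept unaware of waitlist status, say so and describe how.

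The cost is some scheduling burden and one form item, with existing staff. Sample size, treatment and visit schedule do not change. Masking will remain imperfect because children may disclose, completed T2 visits cannot be changed, and the data will mix two assessment procedures, which the report should mention.
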